**Secondary outcomes**		
Clinical state	Demographic, medical and clinical records	Age, education, handedness during activities of daily living, medical history, treatments, disease duration, comorbid diseases or disorders, etc.
	LEDD	LEDD calculated as a sum of each parkinsonian medication
	PFS-16	Fatigue and impact on daily activities
	PDQ-39	Frequency for difficulties because of PD in last month
Cognitive state	MMP	Screening of cognitive function
	FAB	Frontal Lobe function related activities
	BVRT	Visuospatial memory
Neuropsychiatric state	BDI-II	Depression
	HAM-A	Anxiety
	SAS	Apathy
	SEND-PD	Psychosis, apathy, impulse control behaviors
	PPQ	Psychosis (hallucinations/illusions, delusions, spatiotemporal disorientation)
	FrSBe	Behavior related to frontal system dysfunction
	QUIP	Impulse control disorder behaviors
	CNS-LS	Emotional lability
Electromyography	Cortical excitability TMS-EMG measures	Motor thresholds: rMT, aMT, 1 mV threshold (20 t); cSP
**Exploratory outcomes**		
Electrophysiology	Resting-state EEG activity	EEG PSD and connectivity measures, synchronization measures from graph theory metrics.
Neuroimaging	Structural MRI - T1-weitghted (T13D)	Global and regional GM volume changes and CT computation changes
	Resting-state fMRI	Seed-to-voxel and seed-to-seed functional connectivity measures
Serum protein quantification	Single-molecule assay (Simoa; SR-X™ biomarker detection system)	NfL levels
		GFAP levels
		BDNF levels

aMT, active motor threshold; BDI-II, beck depression inventory; BDNF, brain-derived neurotrophic factor; BVRT, Benton visual retention test; CNS-LS, center for neurology study-lability scale; cSP, contralateral silent period; CT, cortical thickness; EEG, encephalography; EMG, electromyography; FAB, frontal assessment battery; fMRI, functional magnetic resonance imaging; FrSBe, frontal systems behavior scale; GFAP, glial fibrillary acidic protein; GM, gray matter; HAM-A, Hamilton anxiety rating scale; LEDD, levodopa equivalent daily dose; MDS-UPDRS, the movement disorder society-sponsored revision of the unified Parkinson’s disease rating scale; MMP, mini mental Parkinson; MRI, magnetic resonance imaging; NfL, neurofilament light chain; PD, Parkinson’s disease; PDQ-39, Parkinson’s disease questionnaire; PFS-16, Parkinson fatigue scale; PPQ, Parkinson’s psychosis questionnaire; PSD, power spectral density; QUIP, questionnaire for impulsive-compulsive disorders in Parkinson’s disease; rMT, resting motor threshold; SAS, Starkstein apathy scale; SEND-PD, scale for the evaluation of neuropsychiatric disorders in Parkinson’s disease; TMS, transcranial magnetic stimulation.

#### Demographic information and clinical records

Medical record: medical history, treatments, disease duration, comorbid diseases or disorders and/or any related information to the medical dimension.Edinburgh handedness inventory (EHI): screening test to ascertain the subjects’ handedness during activities of daily living (ADL; Oldfield, 1971).Modified Hoehn and Yahr Scale (H&Y): a scale used to describe the progression of the disease by descriptive staging. The stages are as follows: (0) no signs of disease, (1) unilateral involvement only, (1.5) unilateral and axial involvement, (2) bilateral involvement without impairment of balance, (2.5) mild bilateral disease with recovery on pull test, (3) bilateral disease with mild to moderate disability and impaired postural reflexes but physically independent, (4) severely disabling disease but still able to walk or stand unassisted, and (5) confinement to bed or wheelchair unless aided (Hoehn and Yahr, 1967; Goetz et al., 2004).

#### Clinical variables

The movement disorder society - unified Parkinson’s disease rating scale (MDS-UPDRS; part II, III & IV) scale: a tool for rating the severity and progression of typical PD symptoms. Only the motor experiences of daily living (II), motor examination (III), and motor complications (IV) subscales will be administered (Goetz et al., 2008; Postuma et al., 2015).Levodopa equivalent daily dose (LEDD): Calculations of the LEDD will be based on a previously reported conversion formula that has been successfully used to determine daily dose equivalents (Tomlinson et al., 2010; Jost et al., 2023).Parkinson fatigue scale (PFS-16): a tool used for the evaluation of the physical aspects of fatigue due to parkinsonism and its impact on the patient’s daily activities. Emotional and cognitive dimensions are not included, as they manifest independently of PD. Two scoring methods are proposed, although we used method 1 (Brown et al., 2005).Parkinson’s disease questionnaire (PDQ-39): the most widely used rating scale for Parkinson’s disease that addresses the frequency with which patients have experienced any difficulties in the last month because of having PD. It contains 39 items organized into 8 dimensions: mobility, activities of daily living, emotional well-being, social stigma, social support, cognition, communication, and physical discomfort (Peto et al., 1995).

#### Cognitive assessment

Mini mental Parkinson (MMP): a brief questionnaire derived from the mini mental state examination and used for the assessment of cognitive function in PD patients. The MMP is composed of seven different sections: temporal and spatial orientation, visual registration, attentional/mental control, two-set verbal fluency, visual recall, shifting, and concept processing (Mahieux et al., 1995).Frontal assessment battery (FAB): a short battery consisting of 6 subtests related to different frontal lobe functions. These functions are as follows: (1) conceptualization and abstract reasoning, (2) mental flexibility, (3) motor programming and executive control of action, (4) sensitivity to interference, (5) inhibitory control, and (6) environmental autonomy (Dubois et al., 2000).Benton visual retention test (BVRT): a test used for the evaluation of visuospatial memory (Benton, 1978). In our protocol, we plan to use the multiple choice format of administration, which consists of stimulus presentation followed by concealment for immediate recognition of one item out of four answer options (specifically, the M form; Le Carret et al., 2003; Amieva et al., 2006).

#### Neuropsychiatric assessment

Beck depression inventory (BDI-II): a self-report questionnaire developed for the evaluation of depressive symptomatology severity. Affective, cognitive, somatic, and vegetative symptomatology are assessed by the 21 items that comprise this inventory. Scores are used to classify individuals as having minimal, mild, moderate, or severe depression (Beck et al., 1996).Hamilton anxiety rating scale (HAM-A): a 14-item clinician-administered rating scale widely used in clinical and research studies to measure the severity of psychic (mental agitation and psychological distress) and somatic anxiety (physical complaints related to anxiety; Hamilton, 1959).Starkstein apathy scale (SAS): a 14-item scale used to screen for and determine the severity of apathetic symptoms. These symptoms are as follows: diminished motivation; other aspects related to the behavioral, cognitive, and emotional spheres of apathy; and insight (Starkstein et al., 1992).Scale for the evaluation of neuropsychiatric disorders in Parkinson’s disease (SEND-PD): a 12-item scale divided into three subscales: psychotic symptoms, mood/apathy, and impulse control behaviors. Items are rated from 0 (not present) to 4 (very severe; Martinez-Martin et al., 2012).Parkinson’s Psychosis Questionnaire (PPQ): a screening tool used to measure the frequency and severity of early signs and psychotic symptoms of PD. These include sleep disturbances, hallucinations/illusions, delusions, and spatiotemporal disorientation (Brandstaedter et al., 2005).Frontal systems behavior scale (FrSBe): a self-report scale designed to assess the changes in behavior that may occur in relation to frontal system dysfunction. The FrSBe is composed of 3 subscales: apathy, disinhibition, and executive dysfunction (Grace and Malloy, 2001).Questionnaire for impulsive-compulsive disorders in Parkinson’s disease (QUIP): a screening questionnaire developed for the assessment of ICDs and related behaviors. The questionnaire is divided into 3 sections. Section 1 assesses four ICDs (gambling and sexual, buying and eating behaviors), Section 2 assesses related compulsive behaviors (punding, hobbyism and aimless wandering), and Section 3 measures compulsive medication usage (Weintraub et al., 2012).Center for neurologic study-lability scale (CNS-LS): a screening instrument composed of seven items that are scored by the patient according to the perceived frequency of pseudobulbar affect (PBA) episodes during the last week (Moore et al., 1997).

#### Electrophysiology

Electroencephalography (EEG) data: resting-state oscillatory EEG activity will be collected using a high-density 128*-*channel EEG system and recorded during a resting-state session of approximately 10 min that includes both eyes-closed and eyes-open conditions. Participants will be instructed to focus on a fixation cross on the center of a desk in front of individuals during the eyes-open condition.Electromyography (EMG) data: several resting-state and active TMS-EMG measures will be calculated for both hemispheres after a single-pulse stimulation is applied over the M1 and collected from the contralateral FDI muscle (see *EMG data analysis* for a detailed description of the analysis that will be performed). The subjects will be instructed to remain relaxed throughout the experiments with the aid of visual feedback from the EMG monitor.

#### Neuroimaging

For all participants, brain MRI data will be collected using a 1.5 T scanner (Siemens Symphony, Erlangen, Germany). The following sequences will be used for data acquisition:

Structural MRI: high-resolution T1-weighted anatomical images will be obtained using a 3D sagittal MPRAGE sequence (TR = 2.200 ms, TE = 3 ms, flip angle = 8°, matrix = 384 × 512 × 176, voxel size = 0.5 × 0.5 × 1 mm).Resting-state fMRI: a T2-weighted functional echo-planar imaging (EPI) sequence sensitive to blood oxygen level-dependent (BOLD) signals will be performed with the following parameters during the eyes-open resting state: repetition time/echo time = 3.000 ms/50 ms, 49 ascending slices, matrix = 64 × 64 × 49, voxel size: 4.06 × 4.06 × 4.05. A total of 120 volumes will be acquired with each scan lasting approximately 7 min.

#### Serum biomarkers

Blood samples from PD patients will be collected via venipuncture at each pre- and post-iTBS timepoint of the study by nurse clinicians from the Department of Neurology at Puerta del Mar University Hospital. All blood samples will be collected in clot-activating serum separator tubes, allowed to clot at room temperature for 30 min, and centrifuged for 10 min at 1,500 g to separate serum from the whole blood. The resulting serum will be aliquoted and properly stored at −80°C until analysis. All participants will have their blood drawn to later quantify serum protein levels of neurofilament light chain (NfL), glial fibrillary acidic protein (GFAP), and brain-derived neurotrophic factor (BDNF).

### Safety assessment

Although existing research on the use of iTBS to treat PD patients has not identified any significant side effects, patients will be carefully monitored for the recognized possible concerns, such as epilepsy. Each treatment and follow-up session, therefore, will include a safety assessment. Other potential reactions, such as fatigue, dizziness, and headache, will be recorded to evaluate the safety of iTBS for PD patients. The most frequent side effects of the EEG recordings are expected to be headache and pain or discomfort in the scalp. Pain and hematoma at the blood sampling site, as well as a vasovagal reaction, syncope, or fainting, may be the most frequent side effects after blood collection. Following each real or sham iTBS phase, safety questionnaires will be administered to the patients, and the results will be recorded and analyzed according to severity, seriousness, and causality. Patients’ vitality, physical health, and mental health will also be monitored to assess any potentially major ill effects.

### Data management

Prior to participation, patients will have to agree to the conditions described in the informed consent form. Agreement to participate can be revoked any time during the course of the experiment. All personal information that might violate the privacy of patients will be codified and entered into a secure database. Copies of paper data forms will be kept behind locks in the research lab. All personal, clinical, and functional data will be properly stored into the DIRAYA platform, a system used in the Andalusian Health Service to support electronic medical records, to which only clinicians have access. Furthermore, analysis of resulting neurocognitive and functional data, such as EEG, MRI, and TMS-EMG data, will be stored in a network-attached hospital storage system to keep extra security copies of imaging data. Blood samples of each patient will be stored and transferred (after obtaining the formal written consent of patients) to the facilities of the Biobank of the Andalusian Public Health System in the Puerta del Mar University Hospital.

### Data collection and analysis

Figure 1 provides a visualization of the complete experimental design including the two phases as well as the washout period and crossover process. Recruitment will be managed by three experienced neurologists who, based on patients’ clinical reports and interviews, will determine their suitability for participation in this investigation. Phase I and Phase II will be identical but differ in terms of groups (i.e., patients who received real iTBS will subsequently receive sham iTBS and vice versa). Patients will be randomly assigned to two equal groups (real or sham) in blocks. Data collection and iTBS sessions will not be performed by the same person to ensure blinding. The full protocol and data acquisition will be performed at the Puerta del Mar University Hospital.

Figure 2 provides a summary of the approximate schedule of patient data acquisition in both phases. Once data are collected, we will determine differences in all outcome parameters before and after intervention and between the real and sham stimulation groups.

**Figure 2 fig2:**
[figure not shown]
Timeline of study-related events during Phase I/II. After randomization, patients will undergo baseline evaluations. This first examination will include clinical, cognitive and neuropsychiatric evaluations; structural and functional resting-state neuroimaging; EMG; EEG; and blood sample collection. These tests will be performed over a maximum of 1 month and prior to the first iTBS session, with the exception of EMG recording (which will be carried out on the same day, immediately before this first session). Once baseline evaluations are completed, patients will undergo iTBS intervention: one daily (real or sham) iTBS session over the bilateral M1 at 80% of the aMT for five consecutive days. Subsequently, the post-iTBS evaluation stage will start with TMS-EMG data acquisition and clinical examination. The rest of the tests will be performed in the following 4 weeks after the last TMS session (week 1: EEG, clinical evaluation, serology and neuroimaging; week 2: cognitive and neuropsychiatric evaluations, clinical evaluation; week 4: last clinical exploration). The same timeline will be followed for Phases I and II.

#### Clinical, cognitive and neuropsychiatric assessments

A neurologist specializing in movement disorders and PD and certified through the MDS-UPDRS Training Program will be responsible for blindly performing all evaluations of the patients’ clinical condition during the different phases of our study protocol. Patients will be assessed at approximately the same time of day to control the effects of medication and, more specifically, to ensure an optimal on-medication state. The neuropsychiatric and cognitive assessments will be performed by two qualified neuropsychologists. The administration of these tests as well as the scoring and correction of data will be performed according to the specific international recommendation for each test and following the Spanish adaptation guidelines. The resulting clinical, neurocognitive, and neuropsychiatric data will be compiled in a database.

#### Electrophysiology data

##### Resting-state EEG activity

Two researchers will be in charge of EEG recordings. High-density EEG data will be collected and recorded using a 128-sponge Ag/AgCl electrode Geodesic Sensor Net (HydroCel GSN, Magstim-EGI, Oregon, United States). EEG signals will be sampled at 1 kHz and recorded using Net Station v. 5.4 software (Magstim/EGI Inc.) with an EGI Net Amps 400 high impedance amplifier. Electrode impedances will be monitored online, and a notch filter will be applied at 50 Hz only for data visualization to remove power line noise. EEG data will be processed offline using the Fieldtrip toolbox (Oostenveld et al., 2011) and custom MATLAB routines (MathWorks, Natick, MA). Briefly, continuous EEG data will be bandpass filtered (0.5–98 Hz) and then segmented into 2-s epochs. EEG signals will be visually inspected, and epochs containing high amplitude artifacts related to participant movements or showing excessive blinks will be rejected. Furthermore, independent component analysis (ICA) will also be conducted to identify and eliminate the components of the EEG signal corresponding to artifacts due to eye movements (saccades and/or blinks) or electrocardiogram activity. The final sample will consist of at least 4 min of artifact-free data. Subsequently, power spectral density (PSD) values will be obtained after fast Fourier transformation (FFT) and averaged to compute an averaged FFT power spectrum for each electrode. PSD values for the delta, alpha, beta, theta, and gamma bands will be analyzed and computed for each treatment phase and stimulation condition.

Individual alpha frequency (IAF) values will be estimated from the mean spectrum over posterior scalp sites by means of peak detection between 7 and 14 Hz. The mean spectral amplitude within the frequency range of the IAF ± 2 Hz (Klimesch, 1999) will be calculated and log-transformed. Thus, PSD values for the following bands will be computed and compared according to each treatment phase and stimulation condition: delta (1–4 Hz), theta (4– to the minimum between 7 Hz and IAF–2 Hz), low alpha (IAF–2 Hz to IAF), high alpha (IAF to IAF +2 Hz), low beta (13–20 Hz), high beta (20–35 Hz), low gamma (35–60 Hz) and high gamma (60–90 Hz; Klimesch, 1999; Babiloni et al., 2020).

Spectral estimates of the relative power of each frequency band during baseline and post-iTBS at any electrode will then be obtained for each participant by subtracting the log-transformed band power during the eyes-closed and eyes-open baseline conditions from the log-transformed band power after treatment, according to the following formula:

Relative frequency band power (*i*) = log (power_i, posttreatment_) – log (power_i, baseline_).

Finally, synchronization measures, such as imaginary coherence (Avena-Koenigsberger et al., 2018) with sensor and source EEG space, will be calculated by obtaining different graph theory metrics to determine the association between graph theory metrics of EEG resting-state brain connectivity and real or sham iTBS treatments. Graph theory measures will be calculated with the igraph package^1^ for the R toolbox (R Core Team, 2018) and Brainstorm software (Tadel et al., 2011; Niso et al., 2019). Resting-state EEG power and EEG connectivity analysis will also be performed by parametric and nonparametric permutation tests to calculate the pre vs. post and real vs. sham differences.

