##### TMS-derived measures of cortical excitability

Two researchers and a neurologist, blinded to group allocation, will be responsible for recording bilateral TMS-EMG data to establish stimulation parameters for the iTBS intervention and determine cortical excitability measures.

Surface EMG data will be recorded after a contralateral single-pulse TMS of the FDI muscle with disposable pregelled Ag/AgCl electrodes (EL503, BIOPAC Systems, Inc., California, United States) in a tendon-belly arrangement. Each participant’s skin will be cleaned with a 70% isopropyl alcohol swab to reduce impendences (<5 kΩ) related to skin conductance.

EMG data will be collected using an EMG amplifier and recorded using a BrainAmp ExG amplifier (Brain Products GmbH, Gilching, Germany). For visual display, we will use some filters (bandpass filter: 10–1,000 Hz, sampling rate: 1 kHz) to remove low-frequency artifacts that occur during stimulation; however, raw data will be recorded. All these measures will be visualized and recorded using BrainVision Recorder 2.1 software (Brain Products GmbH, Gilching, Germany).

For EMG analysis, data will be filtered (bandpass filter of 20 Hz to 450 Hz) and digitized at a rate of 1 Hz. The notch filter will be set at 50 Hz to remove power line interference. Different parameters will be obtained from the electromyography session using Analyzer 2.1.2 software (BrainVision Analyzer, Brain Products GmbH, Gilching, Germany) and custom routines and MATLAB toolboxes.^2^ Subsequently, data will be segmented by markers to delimitate trials. In our case, each single TMS pulse will be a marker. Subsequently, baseline correction and artifact rejection will be performed. Normalized EMG data will be used for subsequent statistical analysis.

The following TMS-EMG parameters of cortical excitability will be obtained after stimulation of the FDI muscle hotspot of the mapping grid:

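### As written, 50 Hz line noise stays in the EEG low-gamma band (35–60 Hz), which would weaken sensitivity in that exploratory outcome

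*Protocol article*

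**What the plan says.** All of this is in the protocol article, mainly under "Resting-state EEG activity".

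- **Notch:** "a notch filter will be applied at 50 Hz only for data visualization"; its stated aim is to suppress mains noise.
- **Offline filter:** "Briefly, continuous EEG data will be bandpass filtered (0.5–98 Hz) and then segmented into 2-s epochs".
- **Epoch rejection:** "epochs containing high amplitude artifacts related to participant movements or showing excessive blinks will be rejected".
- **ICA:** it is used to remove "artifacts due to eye movements (saccades and/or blinks) or electrocardiogram activity".
- **Bands:** the list includes "low gamma (35–60 Hz", with no exclusion around 50 Hz.
- **Outcome measure:** for each band and electrode, the log of post-treatment power minus the log of baseline power. It is compared before versus after treatment and real versus sham.

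The section on TMS-derived measures treats the other electrical signal differently. Its EMG analysis steps state: "The notch filter will be set at 50 Hz to remove power line interference".

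Table 1 lists resting-state EEG among the exploratory outcomes.

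**The concern.** The article expects power-line noise in the EEG, since it names a filter against it, but it confines that filter to the screen. The steps that act on the analysed data deal with movement, blinks, eye movements and cardiac activity. A 0.5–98 Hz band-pass keeps 50 Hz, and 50 Hz lies well inside the low-gamma band. Anyone who carries out the text as it stands would add mains power to neural power before taking the log ratio.

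Two things follow:

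- Mains power that is the same in both sessions sits in numerator and denominator alike and pulls the ratio toward 1.
- Mains power that differs between sessions adds variation that has nothing to do with iTBS.

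With 24 patients planned, either could make a true low-gamma response look like no response.

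**Working it through.** The article states no figure on this point, so there is nothing to reproduce. The check has four steps.

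**1. Does 50 Hz survive the stated processing?** The sampling rate (1 kHz) and pass band (0.5–98 Hz) are the article's. The filter type and order are assumed: Butterworth, order 4. The gain at 50 Hz is then 0.998, so the line passes almost unchanged.

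**2. How many frequency bins are involved?** Epochs of 2 s give bins of 1/2 = 0.5 Hz. From 35 to 60 Hz there are (60 − 35)/0.5 + 1 = 51 bins. Leaving out 48–52 Hz removes (52 − 48)/0.5 + 1 = 9 bins and keeps 42/51 = 82%.

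**3. What happens to the article's own measure?** Let neural band power at baseline be 1 and mains power be r, where r is assumed. Natural logs are used.

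- True neural rise of 20%, constant mains: observed change = log[(1.2 + r)/(1 + r)], against the true log(1.2) = 0.182.
- No neural change, mains doubles between sessions: spurious change = log[(1 + 2r)/(1 + r)], in a single patient.

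| r | Observed change (true 0.182) | Share of truth seen | Spurious change if mains doubles |
|---|---|---|---|
| 0 | 0.182 | 100% | 0 |
| 0.1 | 0.167 | 92% | 0.087 |
| 0.5 | 0.125 | 69% | 0.288 |
| 1 | 0.095 | 52% | 0.405 |
| 2 | 0.064 | 35% | 0.511 |

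A second route gives a similar range of r. Take a background falling as 1/f², scaled to 1 at 50 Hz. It sums to about 61 over the 51 bins. A line with a peak of 10 to 100 times local background, spread by a Hann window, adds 1.5 times its peak, that is 15 to 150. So r = 15/61 = 0.25 to 150/61 = 2.5. These inputs are also assumptions.

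**4. What happens to real versus sham?** A simulation used 24 patients who each receive both conditions, a neural log-SD of 0.15 per session and a mains log-SD of 0.7 per session independent of condition. Both SDs are assumed. The within-patient difference between the real and sham changes was tested two-sided at 5%, in 4,000 simulated trials per setting.

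| Median r | Type I error, no effect | Mean estimate, true 0.182 | Power |
|---|---|---|---|
| 0 | 0.054 | 0.182 | 81% |
| 0.1 | 0.053 | 0.163 | 68% |
| 0.5 | 0.054 | 0.123 | 19% |
| 1 | 0.048 | 0.095 | 10% |
| 2 | 0.053 | 0.067 | 6% |

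With no true effect, the mean real-minus-sham difference was about 0 throughout. The loss is in sensitivity; there is no false treatment effect.

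**The case against.** The strongest reply is that the notch sentence describes acquisition. Keeping the notch off the stored signal preserves the raw data and does not forbid line removal later. The offline pipeline is presented as a summary, it relies on a toolbox and custom routines, and the full protocol is not shown. Naming a 50 Hz notch for EMG does not turn silence about EEG into a prohibition.

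Part of this stands. The article does not say that line removal will be omitted, so a reader may not conclude that mains noise will certainly be in the analysed data. But this is more than a detail left out. The article fixes the role of the notch, the analysis pass band, the artefact targets and the band edges, and together these put 50 Hz inside a named outcome. In the parallel EMG description it separates display filters from analysis filters and puts the notch among the latter.

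A reader might also infer that mains noise distorts the comparison of real with sham stimulation. The documents do not support that. Every patient receives both conditions in randomised order, and noise unrelated to condition leaves that contrast centred on zero when there is no effect. A false difference would need mains pick-up that differs systematically between real and sham sessions, and nothing in the article suggests this. Likewise, the spurious shifts from a doubled line are single-patient figures. A group-level pre/post shift would need mains to move in the same direction across patients.

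Finally, the scope is narrow. Low gamma is one of eight listed bands, high gamma (60–90 Hz) does not contain 50 Hz, and the MDS-UPDRS outcome is untouched.

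**Conclusion.** The point holds as a defect in the stated EEG processing. As written, low-gamma power would include any 50 Hz line noise. That would attenuate a true log power change and add session-to-session variance. It could also shift a within-condition pre/post difference if the mains level changes between sessions. It would not by itself bias the randomised real-versus-sham contrast.

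The size depends on a mains level that the article does not give. With constant mains power at 0.1 to 2 times neural band power, about 92% to 35% of a true 20% change is seen. The loss is minor at the low end of that range and severe at the high end. The power figures rest further on the assumed session SDs and on all 24 patients contributing. The calculation follows the article's formula, which takes the log of band power. No effect on connectivity was calculated.

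This is a minor point, worth settling before analysis because it is cheap and closes an open preprocessing choice.

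**What to change.** Before computing low-gamma power, and any connectivity measure in that band, do one of the following:

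- apply an offline 50 Hz line removal to the analysed EEG; or
- leave 48–52 Hz out of the low-gamma band.

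Choose one in advance and apply it identically in all sessions and both conditions. Correct the resting-state EEG section so that it says how 50 Hz is handled in the analysed signal, as the EMG text does. If offline line removal is already intended, one sentence saying so is enough.

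The cost is one processing step on recordings to which the notch is not applied. No new data are needed. With the second option the band keeps 42 of its 51 bins.

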### Procedure and intervention

Our study will be composed of 2 different phases, Phase I and Phase II, separated by a washout period of at least 3 months. Each phase will consist of 3 stages: baseline evaluation, iTBS intervention, and posttreatment evaluation (Figure 1). The baseline evaluation period will begin once the patients agree to participate in the investigation. From this moment until a maximum of 30 days later, patients will undergo (i) a clinical and motor examination in the ON state, (ii) an extensive cognitive and neuropsychiatric assessment, (iii) a resting-state EEG recording, (iv) structural and functional MRI scans, and (v) blood sample collection. Moreover, immediately following the completion of baseline evaluations and just prior to the start of the iTBS intervention stage, a variety of TMS-EMG cortical excitability measures will be acquired. Once this first stage is fully completed, patients will receive a session of real or sham iTBS over the bilateral M1 once per day for five consecutive days. During the last session of iTBS, TMS-EMG parameters of cortical excitability will be acquired, and patients will undergo a clinical motor evaluation. After the intervention stage, the posttreatment evaluations will be conducted. Subsequently, within a 3–4 day window, resting-state EEG data will be recorded for all participants. A week after the last iTBS session, patients will undergo a second clinical evaluation, and a new blood sample will be collected. Next, on the eighth day posttreatment, structural and functional MRI scans will be acquired. At 2 weeks post-iTBS, a new neuropsychiatric and cognitive assessment will be performed along with a third motor evaluation. Finally, the last visit will occur 28 days after the iTBS intervention, consisting of the fourth and final clinical evaluation (Figure 1). Subsequently, all patients will undergo a washout period of at least 3 months prior to the start of the crossover process and Phase II of the study.

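### High alpha is tied to the individual alpha peak with no rule at the beta border, so it overlaps the fixed low-beta band for any patient whose peak exceeds 11 Hz

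*Protocol article*

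**What the plan says.** The protocol article, under Resting-state EEG activity, estimates each patient's alpha peak "by means of peak detection between 7 and 14 Hz". It then gives a full list of bands with numerical edges. The part that matters here reads "low alpha (IAF–2 Hz to IAF), high alpha (IAF to IAF +2 Hz), low beta (13–20 Hz".

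One border in the list is protected. Theta is defined as "theta (4– to the minimum between 7 Hz and IAF–2 Hz", so theta gives way when a slow alpha peak pulls low alpha downwards. There is no matching rule where alpha meets beta.

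Band power then enters a change score for each band, formed by "subtracting the log-transformed band power during the eyes-closed and eyes-open baseline conditions from the log-transformed band power after treatment". The same section plans parametric and permutation tests of pre versus post and real versus sham. Table 1 lists EEG spectral power and connectivity among the exploratory outcomes.

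**The concern.** Bands that are analysed and reported as distinct should not contain the same frequencies. Here two adjacent bands follow the patient's peak while their upper neighbour is fixed, and the permitted range of the peak is wide enough for them to collide. Where they do, one physiological change enters two change scores. A rise or fall in fast alpha then also shows as a rise or fall in low beta, and the reader cannot tell them apart.

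What is at stake is the labelling of an effect, not whether one is found. If nothing changes at any frequency, shared frequencies create no difference between real and sham stimulation. If alpha does change, the overlap can present it as a beta change as well.

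**Working it through.** The plan gives no figure for this point, so there is none to reproduce. The check is interval arithmetic on the stated edges.

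**Inputs, all from Resting-state EEG activity**
- IAF search range: 7 to 14 Hz.
- Low alpha: IAF−2 to IAF.
- High alpha: IAF to IAF+2, with no upper limit.
- Low beta: 13 to 20 Hz, so 7 Hz wide.
- Table step of 0.5 Hz: epochs are "segmented into 2-s epochs", and 1/(2 s) = 0.5 Hz, assuming no zero-padding. The overlap itself does not depend on this step.

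**Formulas**
- High alpha shared with low beta = max(0, (IAF+2) − max(13, IAF)).
- Low alpha shared with low beta = max(0, IAF − 13).
- Low-beta width if it starts at max(13, IAF+2) = 20 − max(13, IAF+2).

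| IAF (Hz) | High alpha (Hz) | High alpha in low beta | Low alpha in low beta | Share of the 7 Hz low-beta band also counted as alpha | Low-beta width under the proposed rule |
|---|---|---|---|---|---|
| 11 or below | ends at 13 or lower | 0 | 0 | 0 | 7 |
| 11.5 | 11.5–13.5 | 0.5 | 0 | 0.5/7 = 7% | 6.5 |
| 12 | 12–14 | 1.0 | 0 | 1/7 = 14% | 6 |
| 12.5 | 12.5–14.5 | 1.5 | 0 | 1.5/7 = 21% | 5.5 |
| 13 | 13–15 | 2.0 (all) | 0 | 2/7 = 29% | 5 |
| 13.5 | 13.5–15.5 | 2.0 (all) | 0.5 | 2.5/7 = 36% | 4.5 |
| 14 | 14–16 | 2.0 (all) | 1.0 | 3/7 = 43% | 4 |

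The shares are shares of band width, not of power. The share of power depends on the spectrum, which the documents do not give.

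**Two possible repairs compared**
- *Cap high alpha at the lower of IAF+2 and 13 Hz.* High alpha no longer overlaps low beta, but it has zero width at an IAF of 13 Hz or more. Low alpha still runs up to 1 Hz into low beta at 14 Hz.
- *Start low beta at the higher of 13 and IAF+2 Hz.* Both alpha bands end at or below the new edge, so overlap is 0 throughout the 7–14 Hz range. The narrowest low-beta band is 16–20 Hz, at an IAF of 14 Hz. This is the true counterpart of the theta rule, in which the neighbouring band yields and alpha keeps its full width.

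The stated edges also leave unassigned gaps: IAF−9 Hz between theta and low alpha above 9 Hz, and 11−IAF Hz between high alpha and low beta below 11 Hz. For example, each gap is 1 Hz at an IAF of 10 Hz. A gap counts nothing twice and is not part of this point.

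**The case against.** Four arguments can be made on the other side.

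- **The affected group may be small or empty.** This stands. The documents give no distribution of peak frequency, and at 11 Hz or below the overlap is exactly zero. The search range nevertheless admits values up to 14 Hz, so the plan should handle them.
- **The outcome is exploratory.** This also stands. The primary outcome and the sample size are untouched.
- **The band scheme is attributed to published sources.** Those are not at hand, so how they treat the alpha–beta border cannot be checked. The edges printed in the article overlap whatever their origin.
- **An article condenses.** This does not answer the overlap, because the article states the complete list of edges. A fuller document with the same edges would have the same overlap.

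A reader might also infer that the peak is re-estimated in every recording, so that the before–after difference compares different frequency ranges. The documents do not support that as an error. The IAF is "estimated from the mean spectrum over posterior scalp sites", and the text does not say whether that means one recording or each. There are four recordings per patient, since "Each phase will consist of 3 stages: baseline evaluation, iTBS intervention, and posttreatment evaluation" and there are two phases. The EEG session "includes both eyes-closed and eyes-open conditions", which makes 4 × 2 = 8 candidate spectra. Which of them supplies the IAF is a detail that an article may leave to the full protocol or analysis plan.

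Nor would freezing the bands be a clear gain. Illustrative spectra were assumed: a 1/f background plus a Gaussian peak at 8–10 Hz, SD 0.75–1.5 Hz, height 1 to 10 times background. Under these, a 0.5 Hz detection error with bands that follow it changes low alpha by 2% to 39% and high alpha by 10% to 42%. A true 0.5 Hz shift changes either band by at most about 5% when bands follow the peak. With fixed bands the same true shift changes low alpha by −8.5% to −39.7% and high alpha by +7.1% to +38.7%. The choice is a trade-off, and all these sizes rest on assumed spectra.

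**Conclusion.** The point holds as a minor error of definition. Under the stated edges, high alpha and low beta overlap for every IAF above 11 Hz, by half of high alpha at 12 Hz and all of it from 13 Hz. Low alpha joins in above 13 Hz. This follows from the article's own numbers and needs no assumption about the spectrum or about how often the peak is estimated.

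Its practical weight depends on how many patients have a peak above 11 Hz, which cannot be judged from the documents. It is confined to exploratory EEG band power and affects which band a change is attributed to. It does not by itself produce a spurious difference between real and sham. The source recording and eye condition for the IAF are worth clarifying but are not part of the error.

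**What to change.** In the band list under Resting-state EEG activity, start low beta at the higher of 13 Hz and IAF+2 Hz, leaving its upper edge at 20 Hz and the alpha bands as they are. Make the change before any unblinded EEG analysis.

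**Cost.** It is a one-line change in the EEG script and needs no new data. For patients with an IAF above 11 Hz, low beta becomes narrower (down to 4 Hz), and its lower edge differs between patients. Low-beta results should be described accordingly, with the number of such patients stated.

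**Clarification, not correction.** State which recording and eye condition supply the IAF, since the low-beta edge will now depend on it too. Reporting the peak frequency itself alongside band power would help the reader to separate a shift in frequency from a change in power.
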